### Measures

Demographical and clinical data will be collected via a self-report form. Demographical data include gender, age, educational level, marital status, and work status.

Primary outcomes are physical (weight and BMI) and psychological conditions (PGWBI; OQ-45.2; DASS; DERS; DEBQ; AAQ-II) and adherence to a healthy lifestyle. Secondary outcomes are subcomponents of psychological flexibility (BVI, CAQ, I-CFQ, FFMQ). All the outcomes will be collected as follows.

#### Primary outcomes

##### Physical variables

Weight and height will be assessed to calculate body mass index (BMI = kg/m^2^).

##### Psychological conditions

Psychological well-being. The *Psychological General Well-Being Inventory* (PGWBI [27];). The Italian validation of Grossi and colleagues [28] consists of 22 self-administered items rated on a 6-point Likert scale, relative to six subscales that offer a measure of the level of subjective psychological well-being. Subscales are anxiety, depression, positive well-being, self-control, general health, and vitality. The internal consistency of the measure was good, with *α* values of subscales ranged from .61 to .85.

Treatment outcomes. The *Outcome Questionnaire-45.2* (OQ-45.2 [29];). The Italian version [30] is used to assess the effectiveness of clinical interventions. It is a self-report questionnaire composed of 45 items. Subscales are symptoms of distress, interpersonal relations, and social role functioning. The total *α* score obtained in the validated version on a clinical sample is excellent (*α* = .90).

Psychological inflexibility and experiential avoidance. The *Acceptance and Action Questionnaire* (AAQ-II [31];). The Italian version [32] is the most widely used self-reported questionnaire that measures psychological inflexibility and experiential avoidance. It is composed of 10 items, rated on a 7-point Likert scale; the internal consistency of the Italian validated version is good (*α* .83).

Depression, anxiety, and stress. The *Depression Anxiety and Stress Scale* (DASS-21 [33];). The Italian version [34] is administered as a measure of psychological distress. It is a self-report instrument that measures several negative internal states: depression, anxiety, and stress. It consists of 21 items rated on a 4-point Likert scale, ranging from 0 to 3. Internal consistency of the Italian validated version in the clinical sample was excellent with *α* value of total score of .92 and *α* values of subscales ranged from .83 to .91.

Emotional regulation. The Difficulties in Emotional Regulation Scale (DERS [35];). The Italian version [36, 37] is administered to assess difficulties in emotional regulation. This is a self-report questionnaire consisting of 36 items, rated on a 5-point Likert scale ranging from 1 (almost never) to 5 (almost always), which explores the following subscales: non-acceptance of negative emotions, inability to undertake purposeful behavior when experiencing negative emotions, difficulty in controlling impulsive behavior when experiencing negative emotions, limited access to emotion regulation strategies that are considered effective, lack of awareness of one’s emotions, and lack of understanding of the nature of one’s emotional responses. The internal consistency of the validated version on a non-clinical sample was good with *α* values of subscales ranged from .77 to .89. The *α* value of the total score was .92.

Emotional eating. The Emotional eating subscale of the Dutch Eating Behaviors Questionnaire [38]. The Italian version [39] is composed of 13 of 33 items of the DEBQ to assess emotional eating. Items are rated on a 5-point scale (1 = never, 5 = very often). Higher scores reflect higher levels of emotional eating. The internal consistency of the validated version of the emotional eating subscale in the overweight sample was excellent (*α* = .97).

#### Secondary outcomes

##### Subcomponent of the psychological flexibility model

Values. The *Brief Values Inventory* (BVI [40];). The Italian version [41] is composed of 12 items aimed to assess the success in living according to personal values. The internal consistency of the Success subscale is .70 in the Italian validation study.

Committed Action. The *Committed Action Questionnaire* (CAQ [42];). The Italian version [43] is an 8-item self-report questionnaire rated on a 7-point Likert scale, used to assess positive and negative aspects of the ability to engage themselves into committed actions driven by values. The internal consistency of the measure tested on a normative sample was good (*α* = .80).

Cognitive fusion. The *Italian-Cognitive Fusion Questionnaire* (I-CFQ [44];). The Italian version [45] is a 7-item questionnaire administered for the assessment of cognitive fusion. The internal consistency of the Italian version is excellent (*α* = .82).

Acceptance. The subscale “Nonjudge” of the *Five Facet Mindfulness Questionnaire*, described below, is used as a measure of acceptance. The internal consistency of the subscale in the validated version is good (*α* = .86).

Mindfulness. The Five Facet Mindfulness Questionnaire (FFMQ [46];). The Italian version [47] is a 39-item self-report questionnaire used as a measure of mindfulness. It is composed of five subscales: observe, describe, act with awareness, non-react, and nonjudge. The internal consistency of the total scale in the validated version is good (*α* = .86).

In particular, the BVI and the CAQ are administered to assess the Engagement subcomponent of the psychological flexibility model. The I-CFQ and the subscale *Nonjudge* of the FFMQ are administered to assess the Openness subcomponent of the psychological flexibility model. The FFMQ is administered to assess the Awareness subcomponent of the psychological flexibility model.

##### Lifestyle

Indicators of healthy lifestyle recorded using wearable devices are (1) daily minutes of moderate-to-vigorous physical activity, (2) daily total amount of calories, and (3) daily steps.

According to guidelines [48, 49], a healthy lifestyle requires a weekly total amount of moderate-to-vigorous physical activity of 150 min, daily energy intake around 80% of the basal energy expenditure estimated, and a weekly mean of 10,000 total daily steps.

In order to monitor the adherence of a healthy lifestyle after the period of rehabilitation, at discharge, participants will receive a wearable device for daily recording of habits regarding diet and physical activity. Monitoring will last 1 month after discharge.

We do not expect any adverse or unintended effects due to the trial participation. However, in case of any form of psychological discomfort, participants can consult the psychologist responsible for the division. Moreover, in case of any doubts or need for information, the participant can contact the responsible of the study. Once enrolled, patients may withdraw from the study at any stage and this will not affect their future treatment.

The clinical psychologist who will conduct the sessions, the participants, and the observers will be blinded to research aims.

All personal information about participants and records of all patients will be collected and preserved separately, in a secure place, into password-protected files kept for 5 years after the end of the trial.

All data collected will be stored in cloud computing and provided to researchers through a dedicated web platform.

The Medical Ethics Committee of Istituto Auxologico Italiano approved the study.

Schedule of enrolment, intervention, and assessment in the study is presented in Fig. 1.

**Fig. 1 Fig1:**
[figure not shown]
Schedule of enrolment, intervention, and assessment procedures

### Intervention

#### Group Engagement

During this intervention, patients will have the opportunity to increase their motivation to change and encourage the engagement in committed actions, consistent with their life values. Patients are invited to reflect on what is important in their lives, which values make their life worth living, and which actions they could take to live a meaningful life, in accordance with personal values. The use of metaphors and experiential exercises will facilitate the process of exploring personal values, identifying life directions and related behaviors. For example, the 80th Birthday Party metaphor requires participants to imagine there is a party in honor of their birthday and the time comes when people are starting to give speeches and try to answer the question about what they want to hear people at the party say. This exercise helps patients in wondering what person they want to be with themselves and others.

#### Group Openness

Participants attending this intervention are guided to recognize and distance themselves from stressful thoughts, feelings, and sensations. They will learn to read suffering as part of human experience, without self-judgment and self-condemnation. Rather, the psychologist will encourage patients’ assumption of an open and acceptable approach to internal experiences. Throughout the session, the psychologist will help patients to reflect on their usual, but ineffective efforts to solve personal problems, and encourage the adoption of new responsive strategies based on acceptance and defusion from personal distress. An example of a metaphor used is The Passenger on a bus. In this metaphor, patients have to imagine to be a driver bus and his every thought is a passenger that gets on and off the bus. This exercise help patients to accept, defuse from, and reduce the power of their thoughts.

#### Group Awareness

The intervention comprises meditation exercises and experiences aimed to learn how to act intentionally with awareness about personal thoughts and sensations without automatically reacting. Participants are supported to recognize their actions and the context where they occur and learn to choose to respond with action consistent with their values and not automatically. The psychologist will propose breathing exercises, body scan, and other mindfulness experiences. Participants will be encouraged to sitting comfortably, close the eyes, feel themselves in contact with the present moment they are living, paying attention to their breath, noticing the rhythm, and any other aspect of the experience of breathing. Then, the therapist guides the participant’s attention on the body, noting any part of their body from the head to feet and then, the sounds around, any noises that could distract their attention on themselves.

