**Methods:**

A randomized controlled trial will be conducted. Ninety Italian adult inpatients with obesity attending a rehabilitation program for weight loss will be randomly allocated into three experimental conditions targeting respectively each subcomponent of the psychological flexibility model: group Engage focused on values-oriented behaviors, group Openness focused on acceptance and cognitive defusion, and group Awareness focused on being present and aware of thoughts, feelings, and behaviors at every moment. Weight, BMI (kg/m^2^), the Psychological General Well-Being Inventory (PGWBI), the Outcome Questionnaire-45.2 (OQ-45.2), the Depression Anxiety and Stress Scale (DASS-21), the Difficulties in Emotion Regulation Scale (DERS), the Dutch Eating Behaviors Questionnaire (DEBQ), the Brief Values Inventory (BVI), the Committed Action Questionnaire (CAQ), the Italian-Cognitive Fusion Questionnaire (I-CFQ), the Five Facet Mindfulness Questionnaire (FFMQ), and the Acceptance and Action Questionnaire (AAQ-II) will be assessed at the beginning (time 0), at the end of psychological intervention (time 1), and after 3 (time 2) and 6 months (time 3) and 9 months (time 4) from discharge. During the following month after discharge, outpatients will be monitored in their adherence to a healthy lifestyle, using a wearable device.

To assess the effectiveness of the intervention, mixed between-within 3 (conditions) × 4 (times) repeated measure ANOVAs will be conducted to examine changes from time 0 to time 1, 2, 3, and 4 in means of weight, BMI, and means of scores PGWBI, OQ-45.2, DASS, DERS, DEBQ, AAQ-II, BVI, CAQ, I-CFQ, and FFMQ, between three groups.

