Emotional eating refers to eating in response to unpleasant emotional states [10]. Since emotional eating has been associated with elevated consumption of high-calorie and high fat, it does not surprise that emotional eating was found to be strongly related to obesity [11] both in adults and in the younger population [12, 13].

The link between negative emotions and emotional eating has been well-established both in general [14] and in obese population [15]. Many studies suggested that dysfunctional eating habits, such as emotional eating, may emerge as a failure of emotion regulation strategies that allow individuals to regulate their own emotions by modulating their responses [16, 17]. As a result, individuals eat in an attempt to regulate their negative internal states.

The treatment of choice to promote self-regulation skills is Acceptance and Commitment Therapy (ACT [18];). ACT is one of the recent third-wave Cognitive Behavioral Therapies (CBTs) rose in the last 20 years. It is a transdiagnostic approach aimed at promoting psychological flexibility defined as the ability of “being in contact with the present moment fully as a conscious human being and, basing on what the situation affords, changing or persisting in behavior in the service of chosen values” [18]. The promotion of psychological flexibility is based on three subcomponents of the psychological flexibility model: openness, awareness, and engagement. Openness refers to the willingness to develop an open and acceptable attitude toward one’s personal internal states such as thoughts, emotions, and bodily sensations; awareness refers to the ability to act intentionally with awareness about personal thought and sensations, without automatically reacting; engagement refers to engage oneself in committed behaviors related to personal values, that is chosen life directions [19].

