To the authors’ knowledge, only one study [26] has previously explored the specific effect of two subcomponents of the ACT on treatment processes and outcomes in 15 adults seeking mental health treatment, founding that both the modules—one targeting acceptance and defusion, and one targeting values-based activation—produced improvements in psychiatric symptoms and quality of life, as well as improvements in specific therapeutic processes. However, no study has already assessed the specific effect of every single subcomponent of the psychological flexibility model, in weight management.

On the basis of these premises, the aim of the current study is to assess—within the context of a brief ACT-based intervention aimed to promote the adoption and maintenance of healthy lifestyle behaviors in a sample of Italian adult individuals with obesity—the specific effect of each subcomponent of the ACT model on the promotion and, most importantly, the maintenance of a healthy lifestyle.

The intervention will be part of a multidisciplinary 1-month rehabilitation program for weight loss.

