## Methods

### Study design

An equivalent randomized controlled trial (RCT) with parallel groups will be conducted. We will perform a simple randomization with 1:1:1 allocation ratio using a computer-generated randomization (www.randomization.com). Allocation concealment will be ensured since all the patients will generate an anonymous code that will be associated to the randomization’s sequence generated by the program. Researchers will be blinded to the association made.

Since we already assessed the efficacy of an ACT-based intervention compared to a CBT-based intervention in the same context of obesity rehabilitation in a previous study [23], in this study, the aim was to compare the three subcomponents of the psychological flexibility model with each other.

Thus, participant enrolled for the study will be randomly allocated into three experimental conditions, targeting respectively each specific subcomponent of the psychological flexibility model:
Group *Engage*Group *Openness*Group *Awareness*

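### The Awareness arm is described as also teaching values-consistent action, which the protocol assigns to Engage, so a benefit in that arm could not be credited cleanly to awareness

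*Protocol article*

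**What the plan says.** All references are to the protocol article.

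- **Aim.** The Background asks for "the specific effect of each subcomponent of the ACT model". Study design says that "the aim was to compare the three subcomponents of the psychological flexibility model with each other". Study design and Procedures both give each arm a single specific subcomponent.
- **Engage.** The abstract has "group Engage focused on values-oriented behaviors". The Background adds that "engagement refers to engage oneself in committed behaviors related to personal values". The Group Engagement section describes work on personal values and the actions that follow from them.
- **Awareness.** The abstract has "group Awareness focused on being present and aware of thoughts, feelings, and behaviors at every moment". The Background says that "awareness refers to the ability to act intentionally with awareness about personal thought and sensations, without automatically reacting". Neither mentions values.
- **Awareness as described under Intervention.** After a first sentence that follows the Background definition, the Group Awareness section says that participants "learn to choose to respond with action consistent with their values and not automatically".
- **Measures.** Under Secondary outcomes, BVI and CAQ measure engagement. The Statistical analysis section compares both scales across the three groups.
- **Fidelity.** Trained observers attend at least 20% of sessions. Their checklist covers each arm's own planned content and process, and they also note any additional strategies used.

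**The concern.** The trial has no inactive arm and no arm that receives the full ACT model. Every between-arm statement is therefore a statement about one component against another, and it is only as specific as the arms are distinct. If one arm's stated goals include another arm's target, a result in that arm has two possible sources, and no analysis of the collected data can separate them. At stake is the attribution that the Background asks for: whether an Awareness result reflects awareness, or awareness together with some values-directed action. Engage versus Openness is not touched.

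**Working it through.** **1. Placing the statements side by side**

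| Where | Engage | Awareness |
|---|---|---|
| Abstract | values-oriented behaviour | present-moment awareness |
| Background definition | committed behaviour tied to values | intentional, non-automatic action; no values |
| Intervention section | values and the actions that follow from them | mindfulness exercises, plus choosing values-consistent action |

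Only the last cell departs from the one-component-per-arm scheme, and the article does not comment on it.

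**2. Does any named activity carry the extra goal?** The Group Awareness section names breathing work, body scanning, attention to sounds and similar mindfulness practice. No values clarification or action planning is listed, and the birthday-party exercise given for Engage does not appear. The overlap is in a stated learning goal, not in a named exercise.

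**3. What it does to attribution.** Let *a* be the effect of awareness training on some outcome and *v* the effect of any values content delivered in the same sessions. The Awareness arm shows *a* + *v*. No other arm receives *a* alone, so *a* and *v* cannot be separated. If *v* = 0 nothing is lost. The article does not allow *v* to be estimated.

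**4. Direction on the primary outcomes.** Take illustrative effects of Engage 0.5 and Awareness 0.8, and a values share of 0.10.
- True difference: 0.5 − 0.8 = −0.30.
- Values content added to full mindfulness training: 0.5 − (0.8 + 0.10 × 0.5) = −0.35, which is wider.
- Values content replacing mindfulness: 0.5 − (0.9 × 0.8 + 0.1 × 0.5) = −0.27, which is narrower.

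The sign depends on how the sessions are built, so no direction follows.

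**5. Can a power loss be put on it?** The plan's own figure is N = 90 for a 3 × 4 ANOVA with f = 0.20, alpha 0.05 and power 0.80. For the interaction, λ = f² × N × 4 / (1 − ρ), with 6 and 261 degrees of freedom. At ρ = 0, λ = 0.04 × 90 × 4 = 14.4 and power is 0.81. At ρ = 0.5, λ = 28.8 and power is 0.99. The article states neither ρ, nor the dropout allowance, nor which ANOVA effect was sized, so the figure can be neither confirmed nor refuted. The point does not depend on it.

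Now assume that Awareness conveys a fraction *c* of the Engage effect on BVI and CAQ, and that awareness and openness training have no effect of their own on these scales. Then f(c) = 0.20 × √(1 − c + c²), and the pairwise Engage-versus-Awareness difference is multiplied by (1 − c). The pairwise start is either d = 0.98 SD (solved from f = 0.20 with only Engage changing, by the same amount at all three later times: d² × 2/9 × 3/16 = 0.04) or d = 0.72 SD (about what 30 per arm detects with 80% power, normal approximation).

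| | c = 0 | c = 0.10 | c = 0.25 |
|---|---|---|---|
| Interaction, ρ = 0.5 | 0.99 | 0.98 | 0.97 |
| Interaction, ρ = 0 | 0.81 | 0.77 | 0.71 |
| Pairwise from d = 0.98, ρ = 0.5 | 0.996 | 0.985 | 0.93 |
| Pairwise from d = 0.98, ρ = 0 | 0.90 | 0.83 | 0.68 |
| Pairwise from d = 0.72 | 0.80 | 0.71 | 0.55 |

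At c = 0.10 the loss in power ranges from about 0.01 to 0.09, depending on the starting assumptions. For scale, two sessions of about 1 h give 120 minutes, so with a linear dose effect (also assumed) c = 0.10 would mean 12 minutes of values work. Since *c*, ρ, the time pattern, the starting difference and the zero own-effects are all assumed, the table shows sensitivity and does not measure a loss.

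**The case against.** The strongest reply is that one subordinate clause is being read as arm content. The Background defines psychological flexibility as a whole by "changing or persisting in behavior in the service of chosen values", so the clause may only say what awareness is for, and it takes participants' values as given. All the named exercises fit that reading. This stands in large part, and it is why the overlap is probably small. It does not remove the point: the clause is listed among the things participants learn, and a therapist or observer working from it could treat it as planned content.

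One could answer that a goal common to the whole model should also appear under Group Openness, where it does not. That is thin evidence, because these are one-paragraph summaries and silence in one does not show that the arms differ.

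A second reply is that fidelity monitoring covers this. For unplanned values work in observed sessions it does. Planned values work might be scored as the Awareness arm's own content, but the checklist is not shown, so this is an inference.

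A third reply is that awareness training may itself help people act on their values, so movement on BVI and CAQ in that arm need not be contamination. This also stands. It is why a reader who infers that the Engage-versus-Awareness contrast on these scales must shrink, or that the trial loses power, goes further than the documents allow.

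**Conclusion.** The point holds as an inconsistency in stated arm content that weakens attribution. The Awareness description includes a goal that the article elsewhere assigns to Engage and leaves out of its own definition of awareness. The consequence is conditional on delivery: to the extent that values-directed action is taught in those sessions, neither a benefit in that arm nor a change there on BVI and CAQ can be credited cleanly to awareness.

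The size is unknown and probably small. A reader might also infer that the primary comparisons are biased in a known direction; the worked example gives both signs, so they are not shown to be. The conclusion rests on the article's wording alone, since session scripts are not shown.

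**What to change.** 1. Remove the values-directed action goal from the Awareness sessions and keep the Background definition of awareness, which is intentional action without automatic reaction.
2. Have the existing observers score all three components in every observed session of every arm, whether the content was planned or not, so that the separation of the arms can be shown.
3. If the goal is kept, describe the arm as awareness plus values-consistent action and limit its conclusions to that combination.

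The cost is one edit to the Awareness session content and one to the observer checklist. The downside is a slightly narrower Awareness session (or a narrower claim for that arm) and a slightly longer checklist. No extra patients, visits or staff are needed.
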